### Statistical analysis

All analyses will be performed according to the Intention to Treat Analysis (ITT) method. Therefore, all participants who entered the study (regardless of whether they completed the 8-week study period) are included in the analysis. Missing data will be checked by multiple imputations. Statistical analysis will be conducted using the SPSS software (Version 24, SPSS Inc., and Chicago, IL, USA). The scatter diagram, histogram, and Kolmogorov–Smirnov test will be applied to examine the normality of the data. Normally distributed variables will be reported as the mean and standard deviation, while the median and interquartile range (IQR) will be used for reporting non-normally distributed variables. Moreover, we will use the chi-square test and Fisher’s exact test to compare categorical variables. Also, the independent sample *t*-test and Mann–Whitney U test will be applied to compare continuous variables between-group, whereas we will use paired sample *t*-test and Wilcoxon rank-sum test for within-group comparisons. To compare the differences in primary and secondary outcomes between the two study groups at the end of the trial and adjust the final findings for potential confounders, we will apply the mixed linear effect model. To correct for multiple comparisons and reduce alpha error, *q* values will be used using the Benjamin-Hochberg method. Based on this, significance was defined in *P* values less than 0.05 and *q* values less than 0.1. Cohen’s *d* will be calculated based on the mean and standard deviation. The effect sizes 0.20, 0.50, and 0.80, respectively for low, medium, and high therapeutic effects of the dietary intervention will be determined. No subgroup analyses are planned. However, no interim analyses are planned for this trial.

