### Outcomes

#### Primary and secondary outcomes

The primary outcomes in this study will be body weight and insulin resistance. However, fasting blood glucose (FBS) levels, lipid profile, insulin levels, homeostatic model assessment for insulin resistance (HOMA-IR), HOMA for β-cell function (HOMA-β), quantitative insulin sensitivity check index (QUICKI), sex hormone-binding globulin (SHBG), dehydroepiandrosterone (DHEA), AMH, free androgen index (FAI), hirsutism, acne, total antioxidant capacity (TAC), total oxidant status (TOS), C-reactive protein (CRP), body mass index (BMI), mental health, sleep quality, appetite, eating behavior, food craving, energy intake, systolic, and diastolic blood pressure will be known as secondary outcomes. All outcomes of this study will be evaluated in pre-and post-intervention.

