### Sample size calculation

By consideration of a type I error of 5% (*α* = 0.05), a power of 80%, according to the mean weight loss of 2.5 kg (a minimum clinically important difference) as the principal outcome and the standard deviation of 3.87 and 3.04 [59], the sample size was computed to be 25 for each group based on the two-sided t-test. Primary outcomes will be measured as a change from baseline. To compensate for an approximate drop-out rate of 5% during the study period, we elevate the final sample size to 30 subjects in each group. To calculate the required sample size Gigacalculator software was used.$$n=\frac{{\left({z}_{1-\frac{a}{2}}+{z}_{1-\beta }\right)}^{2}\left({{s}_{1}}^{2}+{{s}_{2}}^{2}\right)}{{\Delta }^{2}}$$

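### The within-group non-parametric test is named as the Wilcoxon rank-sum test, an independent-samples test, although the before-after data are paired; probably a slip for signed-rank (minor)

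*Protocol article*

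**What the plan says.** All statements are in the protocol article.

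- Statistical analysis, between groups: besides the independent-samples t-test, the "Mann–Whitney U test will be applied to compare continuous variables between-group".
- Statistical analysis, within groups: besides the paired t-test, the "Wilcoxon rank-sum test for within-group comparisons".
- Primary and secondary outcomes: "All outcomes of this study will be evaluated in pre-and post-intervention". Each participant is therefore her own comparator in a within-group test.
- Statistical analysis, main comparison: to compare primary and secondary outcomes between groups and "adjust the final findings for potential confounders, we will apply the mixed linear effect model".

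The article does not name the signed-rank test anywhere, and nothing elsewhere in it corrects the within-group test.

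**The concern.** Wilcoxon rank-sum and Mann–Whitney U are two names for one procedure, which compares two independent samples. One sentence therefore assigns the same independent-samples test to two data structures: different women in different arms, which it suits, and the same women before and after treatment, which it does not.

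Applied to before-after data, the test discards the link between a woman's two values and uses a null variance that assumes they are unrelated. If the values are positively correlated, that variance is too large and the p-values are too large with it. Normally distributed outcomes would be tested with the pairing and non-normal ones without it, so within-arm results would not be comparable across outcomes.

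At stake is the reporting of within-arm change for whichever variables fail the normality check. The article gives no distributions, so which variables these will be is unknown.

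**Working it through.** The plan gives no figure for this point, so there is none to reproduce. The check has two parts.

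**1. The test against the data structure**

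| Comparison | Data | Parametric test named | Non-parametric test named | Matching non-parametric test |
|---|---|---|---|---|
| Between groups | independent | independent-samples t | Mann–Whitney U | Mann–Whitney U (= rank-sum) |
| Within group | paired | paired t | rank-sum (= Mann–Whitney U) | signed-rank |

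Only the last cell of the plan's scheme is wrong.

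**2. Size of the effect if the text is followed literally**

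Inputs:
- Pairs per arm: 30, the planned arm size in Sample size calculation, taken as complete.
- Test level: two-sided 0.05, from the same section.
- Pre-post correlation ρ: not in the documents; assumed 0.3 to 0.9, with 0 as a reference.
- Shift: not in the documents; assumed 0.3 and 0.5 SD, where SD is that of a single measurement and not of the change.

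*Approximate size by formula.* With no change, the difference between the two means has variance 2σ²(1−ρ)/n, while an unpaired test assumes 2σ²/n. The standardised statistic then has standard deviation √(1−ρ), and the true size is about 2Φ(−1.96/√(1−ρ)). This holds for a comparison of means and is a close guide for the rank test.

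- ρ = 0.3: 1.96/√0.7 = 2.34, size about 1.9%
- ρ = 0.5: 1.96/√0.5 = 2.77, size about 0.6%
- ρ = 0.7: 1.96/√0.3 = 3.58, size about 0.03%
- ρ = 0.9: 1.96/√0.1 = 6.20, size effectively 0

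*Simulation.* Bivariate normal data, 30 pairs, 10,000 runs per setting. Each cell gives the percentage of runs rejected, rank-sum / signed-rank.

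| ρ | No change | 0.3 SD shift | 0.5 SD shift |
|---|---|---|---|
| 0 | 4.9 / 5.0 | 20 / 20 | 44 / 44 |
| 0.3 | 1.9 / 4.7 | 14 / 24 | 44 / 59 |
| 0.5 | 0.8 / 4.8 | 12 / 34 | 44 / 74 |
| 0.7 | 0.1 / 4.8 | 8 / 52 | 43 / 92 |
| 0.9 | 0.0 / 5.0 | 3 / 94 | 44 / 100 |

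The two tests agree only at ρ = 0. At ρ = 0.5 the formula gives a size of 0.6% and the simulation 0.8%, so below 1% either way.

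The rank-sum power stays near 44% at 0.5 SD for a simple reason. The expected unpaired statistic is about 0.5/√(2/30) = 1.94, almost at the critical value of 1.96, so its spread hardly matters. At 0.3 SD it is 0.3/√(2/30) = 1.16, well below 1.96, and the narrower spread at high ρ pulls power down.

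The data simulated above are normal, whereas the test would be used on non-normal variables. With log-normal data at ρ = 0.7 and a 0.3 SD shift, power was 8% against 49%, close to the normal result.

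**The case against.** The strongest reply is that this is a slip of terminology. The sentence sets out two matched pairs of tests, names Mann–Whitney U separately for between-group use, and puts the Wilcoxon test next to the paired t-test. The authors plainly recognise that the within-group data are paired and very probably meant signed-rank. That stands, and it makes every consequence above conditional on the text being run as worded. It does not remove the need for the correction, because the text as printed names the wrong test and nothing else in the article overrides it.

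Several stronger readings are tempting but lack support:

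- **That the error produces false positive findings.** Under positive correlation the rank-sum test rejects too rarely, so the cost is power.
- **That it undermines the trial's main inference.** The comparison of primary and secondary outcomes between groups is assigned to the mixed model, and the hypothesis in the Discussion is a comparison with the calorie-restricted control. Neither uses this test.
- **That the test would have almost no power.** Power of 3% to 14% applies to an assumed shift of 0.3 SD at correlations of 0.3 to 0.9. At 0.5 SD it is about 44%, a real loss but not a collapse.
- **That the affected p-values would distort the q-value correction, or that efficacy will be claimed from within-arm change.** The article says neither. The q-value statement directly follows the mixed-model sentence, and which tests belong to the correction family is detail an article may leave to the full protocol or analysis plan.

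**Conclusion.** The point holds as a minor one. The plan names an independent-samples test for paired data, probably by a slip. Followed literally, it would make within-arm p-values for non-normal variables conservative. With 30 pairs, the true size falls from 5% to about 2% at a correlation of 0.3, below 1% at 0.5 and about 0% at 0.9. Power for a 0.5 SD shift is about 44%, against 59%, 74%, 92% and 100% for signed-rank at correlations of 0.3, 0.5, 0.7 and 0.9.

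These sizes rest on assumed correlations and shifts that the documents do not give; only the sample size and test level come from the protocol. The mismatch between test and data needs none of these assumptions. A reader might infer that the trial's between-group conclusions are at risk. They are not, because those comparisons do not use this test.

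**What to change.** In the Statistical analysis section, replace Wilcoxon rank-sum test with Wilcoxon signed-rank test for the within-group comparisons. Leave the Mann–Whitney U test for between-group comparisons as it is.

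The cost is one word. Design, data collection, sample size and the mixed model do not change, and SPSS, the software the plan names, offers the signed-rank test. The correction should be made before the analysis is run.

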### Consent

When participants sign the consent form, they will be asked if they consent to their data being used in the event of withdrawal. Also, researchers will ask participants for permission to share relevant data with people from the participating universities or regulatory authorities. Biological specimens are not collected for storage in this trial.

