### Adherence to the intervention

All subjects will receive telephone calls per week and monthly meetings with a dietitian during the intervention to encourage adherence to the diet. We will send a daily reminder via instant messages that inform them when to stop eating and when they are allowed to eat. Furthermore, periodic meetings (once every 30 days) should be promoted for participants to share their experiences and receive support from physicians. Moreover, all people are given detailed written and oral instructions for each meal plan, and as mentioned, there is no difference between people participating in the fasting diet and the low-calorie diet. Monitoring of food programs is done through the daily interaction of the researcher and the participant in the project through phone conversations. If they do not attend more than two consecutive phone sessions or consume 3 inappropriate meals or fail to follow the diet instructions 3 times a week for more than 2 consecutive weeks is considered non-compliant patients [44, 45]. A 3-day 24-h dietary recall will be taken from the participants every 2 weeks to confirm compliance.

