##### Anthropometric and blood pressure assessment

Body weight will be measured by fasting, without shoes, with minimal clothing, and using a digital scale (Seca, Hamburg, Germany) with a precision of 100 grams at baseline and 8 weeks during the intervention. The height of people will be measured to the nearest 0.5 cm while standing without shoes. BMI will be calculated using the formula of dividing weight in kilograms by the square of height in square meters. To measure blood pressure, patients were asked to rest for 10 min, then the measurement will be done using a mercury sphygmomanometer (Riester, Germany). The blood pressure of each person will be measured twice with a time interval of 10 min, in a sitting position. The average of these two measurements is considered as the patient's blood pressure.

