##### Biochemical assessment

Blood samples will be collected from the participants in the intervention on the first day and at the end of the intervention, observing 12–14 h of fasting. A 10-ml blood sample without any anticoagulant is centrifuged at a speed of 3500 rpm for 10 min. The serum separated from each person’s blood sample is transferred into sterile microtubes. The microtubes will be stored at − 80 °C.

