### Data management and monitoring

In the baseline and post-intervention phases, data will be collected. CRFs (case report forms) will be used for recording participant data. Data entry and management will be done using an electronic database after CRFs are used for data collection. There will be two data collectors, and completed clinical raw data will be sent for approval to the project supervisor. Documentation is kept in a locked drawer, only accessible by the principal investigator. The forms contain an ID number unique to the participant and do not contain any information that can be used to identify the patient.

A clinical trial monitor occasionally supervises the study progress and ensures patient rights and well-being are safeguarded; the protocol, ethical requirements, standards, and regulations are being followed; the essential documentation is available; and collected data are accurate as there were recorded. One of the investigators will check the coding, security, and storage of data. In addition, she will evaluate data entry and data values twice. If any participant reports the occurrence of adverse events, more information is required to make a decision about excluding the participants from the trial. Unblinding is permissible in this situation based on the Medical Ethics Committee criteria. Ethical review of the data will be overseen by the Tehran University of Medical Sciences. Further, patients who discontinue the study or deviate from it will be provided with a list of all outcome data. Missing data will be imputed using modern methods for dropouts.

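### The ITT statement makes no exception for refused data, and the plan does not say which outcomes are collected from women who stop before week 8

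*Protocol article*

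**What the plan says.** All references are to the protocol article.

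- **Analysis set (Statistical analysis).** Analyses are by intention to treat, and "all participants who entered the study (regardless of whether they completed the 8-week study period) are included in the analysis". No exception is given. Missing data are handled by multiple imputation.
- **Consent.** On signing, "they will be asked if they consent to their data being used in the event of withdrawal". The section does not say what follows a refusal.
- **Timing of the primary outcomes.** Primary and secondary outcomes: "All outcomes of this study will be evaluated in pre-and post-intervention". Anthropometric and blood pressure assessment: weight is taken "with a precision of 100 grams at baseline and 8 weeks during the intervention", fasting and in minimal clothing. Biochemical assessment, which supplies insulin resistance: "Blood samples will be collected from the participants in the intervention on the first day and at the end of the intervention".
- **Women who stop (Data management and monitoring).** The only sentence on them reads that "patients who discontinue the study or deviate from it will be provided with a list of all outcome data".
- **Contacts and data in between.** Adherence to the intervention plans weekly calls, monthly meetings with a dietitian, and a 3-day dietary recall every 2 weeks. It names no weighing at the meetings. Assessment of physical activity plans records in weeks 1, 2, 4, 6 and 8.

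**The concern.** Asking in advance about data use has meaning only if a refusal is honoured. The analysis section nevertheless includes everyone, and nothing links the two statements. If refused data are dropped without mention, the result is reported as ITT on a set that is partly self-selected.

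The second part is what the imputation has to work with. Both primary outcomes are changes over two time points. A woman who leaves in week 5 and is not seen again has no post-baseline weight and no post-baseline insulin-resistance value. The sentence that should say what is collected from her describes, read literally, something handed to the patient. The document therefore leaves open whether week-8 outcomes are sought from women who stop. The diets are not blinded, so stopping could differ by arm and be related to weight change. Imputation that rests mainly on baseline would then make stoppers resemble the completers of their arm.

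**Working it through.** **1. The two statements side by side.**

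| Case | Used under the ITT sentence? | Used under the consent answer? |
|---|---|---|
| Completes, either answer | yes | yes |
| Withdraws, agreed | yes | yes |
| Withdraws, refused | yes | no |

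They conflict only in the last row.

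**2. How many women.** Inputs from Sample size calculation: 25 per group needed, 30 enrolled, 5% loss; three groups, so 90 women. Inflating 25 for 5% gives 25 / 0.95 = 26.3, so 27. The 30 enrolled would absorb (30 − 25) / 30 = 16.7%. I take the 25 as stated; whether it follows from the printed formula is a separate matter.

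- Planned loss: 0.05 × 30 = 1.5 women per arm; 0.05 × 90 = 4.5 in all.
- Loss of 16.7%: 5 per arm, 15 in all.

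The documents give no refusal rate, so the number absent from the ITT set is shown over a range (withdrawals × share who refused):

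| Share refusing | 5% loss | 16.7% loss |
|---|---|---|
| 0% | 0 | 0 |
| 25% | 1.1 | 3.8 |
| 50% | 2.3 | 7.5 |
| 100% | 4.5 | 15 |

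**3. Effect of treating stoppers as completers.** Let p be the proportion lost in an arm and g the amount by which stoppers lose less weight than completers. Shift in that arm's mean = p × g. Assume g = 2.5 kg. This equals the whole target difference and is not a figure the documents give for stoppers.

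- 5%: 0.05 × 2.5 = 0.125 kg (5% of 2.5 kg)
- 10%: 0.10 × 2.5 = 0.25 kg (10%)
- 16.7%: (5/30) × 2.5 = 0.42 kg (17%)

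These are single-arm shifts. With the same g in both arms, the bias in the contrast is (p1 − p2) × g. It is 0 at equal loss, (0.10 − 0.05) × 2.5 = 0.125 kg at 10% against 5%, and (0.167 − 0.05) × 2.5 = 0.29 kg at 16.7% against 5%.

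**4. What an interim weight would add.** Assume a day-30 weight change correlates 0.70 to 0.85 with the week-8 change. It would then explain 0.70² = 0.49 to 0.85² = 0.72 of the variance of the missing value, but only for women who leave after the meeting.

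**5. What the plan already has.** If the 2-weekly recalls are counted from the start, a woman who leaves in week 5 would have recalls from about weeks 2 and 4, and activity records from weeks 1, 2 and 4. These can serve as auxiliary variables, but none is a weight.

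**The case against.** A reader might infer that the ITT promise cannot be met at all. The documents do not support that: it fails only for a woman who both refuses and withdraws. If no such woman occurs, the set is complete. Asking the question is an ordinary ethical safeguard, and it also secures permission to keep the data of those who agree. This stands, and it is why the consent question should stay.

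A reader might also infer that women who stop contribute no outcome information. That goes too far. Stopping the diet or capsules is not withdrawing consent, and nothing in the article bars a week-8 measurement. Energy intake is a listed secondary outcome, and the recalls supply it up to the time of leaving. Two measurement times do not rule out ITT with multiple imputation; they make it lean more on its assumptions.

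It can fairly be said that the kilogram figures rest on an assumed gap and largely cancel if loss is similar across arms. It is also true that no text says the dietitian meetings are fasted or have the study scale. Both points stand and limit the claimed gain.

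The Exclusion criteria, under which participants are excluded for low adherence and other reasons, are a firmer conflict with ITT. That is a separate matter. Settling it would not settle refused data or what is measured in women who leave of their own accord.

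**Conclusion.** The point holds in limited form. The unqualified ITT statement and the consent option need reconciling. The sentence on women who discontinue or deviate does not do its job. Neither primary outcome has a planned interim value. At the planned 5% loss this concerns 1 to 2 women per arm, with a shift of about 0.13 kg in one arm's mean under the assumed 2.5 kg gap. The between-arm bias may be smaller or nil, and grows only as loss differs by arm. This is an inexpensive improvement to the promised analysis, not a flaw that invalidates it.

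**What to change.** 1. **Data management and monitoring.** Replace the sentence on women who discontinue or deviate. State that week-8 outcomes, at least weight, are sought from every woman who stops or deviates unless she withdraws consent to follow-up.
2. **Adherence to the intervention and Anthropometric assessment.** Record weight at the existing monthly dietitian meeting, under the same conditions as the baseline weight where feasible and otherwise marked as non-fasted. Use it as an auxiliary variable in the multiple imputation.
3. **Statistical analysis and Consent.** Keep the consent question, state that the ITT set is subject to it, and report refusals among withdrawals by arm.

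**Cost.** A few minutes and one CRF field per participant, and possibly a fasted morning meeting. Item 2 helps only for women who leave after about day 30. The Trial status section expected recruitment to be almost finished on 23 September 2023, and the article appeared on 25 October 2023. Items 1 and 2 therefore help only women still in follow-up. Item 3 changes text and reporting and can still be done for the whole trial.

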## Discussion

PCOS is a complex endocrine disorder characterized by ovulatory dysfunction, hyperandrogenism, and other metabolic disorders [60]. Disturbance in the body’s circadian clock rhythm and the imbalance of intestinal microbial composition and increased insulin can play a pivotal role in the pathogenesis of PCOS [15]. In recent years, lifestyle modification, dietary interventions, and the modification of intestinal microbial have been touted for helping to improve patients with PCOS [4]. Human and animal studies showed that the IF diets may be a promising intervention strategy through the effect on the body’s circadian clock, intestinal microbial composition, and regulation of metabolism can help reduce body weight, increase fat oxidation, improve insulin resistance, and reduce inflammation [61]. One form of IF is TRF, which is more adherent than other forms of IF [13, 14]. Although most human clinical trials of TRF did not explicitly restrict caloric intake and/or recommend any dietary recommendations, participants in the freely consumed TRF group typically reduced their caloric intake by 7–22% [62, 63]. In other words, TRF can influence energy expenditure to obtain a negative caloric balance [14]. However, there is surprisingly little empirical data to support the notion that reducing or eliminating food after a certain time of night leads to lower daily energy intake or effective weight management in healthy adults [64]. TRF studies show that increasing the duration of daily fasting to periods of more than 12 h may bring more cardiometabolic benefits [65]. However, daily fasting for 16 h or more usually requires skipping a meal, which can reduce adherence or lead to poorer food choices [66]. For this reason, some studies used the TRF diet with 14 h of fasting to increase the adherence of participants [62, 63, 66–69]. Emerging evidence has proposed that an early TRF diet (food consumption in the early hours of the day) compared to a delayed TRF (food consumption in the last hours of the day) was effective for improved glucose tolerance, body weight control, and cardiometabolic effects [70, 71]. Indeed, the mechanism of favorable effects of early TRF is related to central and peripheral circadian oscillators. So that eating between 8:00 am and 6:00 pm optimizes the functioning of the organs and the environment involved in metabolism, and because the time of eating corresponds to the fluctuations of metabolic hormones, it can prevent the development of metabolic diseases and diabetes [71].

Patients with PCOS have significant changes in the composition of the gut microbiota. This change was associated with a decrease in α diversity and changes in β diversity [22]. There is growing evidence that gut microbiota dysbiosis is related to sex hormone levels, estrous cycles, and ovarian morphological changes [23]. Based on a large amount of data, the administration of probiotics protects the intestinal barrier, consequent in the formation of short-chain fatty acid metabolites (SCFAs) [29]. It can show unique effects for reducing insulin resistance, inflammation, and modulating androgen levels [25]. *Lactobacillus rhamnosus* supplementation enhanced the effectiveness of weight loss therapy for obese women, as demonstrated by Hulston et al. [29]. Also, *Lactobacillus reuteri* was shown to improve glucose tolerance in rats with constant darkness-induced PCOS in a previous study [33]. In addition, clinical trials have shown that *Lactobacillus rhamnosus* and *roteri* can play a positive role in restoring the vaginal microecology and treating bacterial vaginosis. So, correcting the microbial condition of the vagina by improving the menstrual cycle and AMH level leads to improvement in fertility [72]. Probiotics may have additional benefits to increase efficacy for weight control and improve cardiometabolic status when combined with an IF intervention or other CR diet [36, 73].

We hypothesized that 10-h TRE administered alone or in combination with probiotic supplementation to overweight and obese PCOS subjects would lead to weight loss and improved metabolic, hormonal, inflammatory, and antioxidant markers compared to control subjects following a standard 3-meal-per-day CR diet. To the best of our knowledge, no clinical trial has investigated the effect of IF diet combination with probiotics supplementation in patients with PCOS. Therefore, the present study aims to investigate the effects of IF alone or in combination with probiotic supplementation compared to the CR diet on anthropometric measures, metabolic status, inflammation, and oxidative stress in women with PCOS. If successful, nutritionists in clinical environments may recommend a new eating pattern (TRF) alone or along with probiotic supplements for patients with PCOS to treat this common disorder.

